**Figure 1 F1:**
[figure not shown]
A flow chart of the study. ABI = ankle-brachial index, baPWV = brachial-ankle pulse wave velocity, BMI = body mass index, BP = blood pressure, Visit 1 = 7 days after screening, WC = waist circumstance.

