### Intervention

2.6

Since this is an observational study, the treatment to improve circulatory disturbance is not restricted during the study. For a given period, treatment with Korean medicine, other Korean medical treatment, and prescription medication other than Korean medicine should be recorded. For Korean medicine, the name of the medicine, medicine composition, and treatment duration should be recorded.

For participants enrolled in the study after screening, we will perform blood tests; ABI and brachial–ankle pulse wave velocity measurement; blood stasis diagnosis questionnaire assessment; blood pressure, body mass index, and waist circumference measurement; and concomitant drug and Korean medical treatment assessment at visit 1 within 7 days of registration.

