#### Primary outcome

2.7.1

1.Resistin, serum amyloid P component, C-reactive protein, and D-dimer are the candidate indicators that seem effective in diagnosing blood stasis based on previous studies on blood stasis.^[12–15]^2.Blood stasis score: A blood stasis questionnaire used to assess the presence/absence of blood stasis and to evaluate the blood stasis score was developed by the Korea Institute of Oriental Medicine through a blood stasis diagnosis technique development research project.^[16–18]^ It was executed for 5 years from 2013 to 2018, and it showed high reliability and validity.^[17,18]^ We extracted 31 questions related to metabolic disorders from the blood stasis questionnaire using the experts’ delphi method and validity analysis, in order to use it as an assessment tool in this study.^[19]^ By referring to the standard operating procedure of each question, a Korean medicine doctor will directly interview each patient and complete the blood stasis questionnaire (Supplemental Digital Content (Appendix 1)).

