### Statistical analysis

2.10

A basic analysis of the study results will compare the difference in evaluation indicators of groups I and II (with circulatory disturbances) with that of group III (without circulatory disturbances) at visit 1. All statistical analyses will be subjected to two-tailed tests, and the significance level will be set at 5%. A descriptive analysis of the evaluation items and blood indices for each group will be conducted to represent the categorical variables as n (%) and continuous variables as mean ± standard deviation. To compare the intergroup differences for the obtained outcome value for each item, categorical variables will be subjected to the chi-square test and Fisher exact test, whereas continuous variables will be analyzed using the *t* test and analysis of variance or nonparametric methods such as Mann-Whitney *U* test and Kruskal-Wallis test for those not meeting the normality criteria. Analysis of covariance will be performed when it is necessary to control underlying variables, such as demographic variables (sex, age, weight, and height). For data with a missing value, the last observation carried forward will be used through CRF inspection to replace the missing value.

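### Last observation carried forward does not fit a visit-1 comparison: the four biomarkers have no earlier value to carry, and for the four grouping measures it would probably reuse the selection value

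*Protocol article*

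**What the plan says.** All references are to the protocol article.

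- **Missing data (section 2.10).** One rule is given, with no restriction by variable or visit: "For data with a missing value, the last observation carried forward will be used through CRF inspection to replace the missing value".
- **Analysis time point (section 2.10).** The evaluation indicators of groups I and II are compared "with that of group III (without circulatory disturbances) at visit 1". No other time point is named for analysis.
- **Timing of visit 1.** The Figure 1 caption has "Visit 1 = 7 days after screening". Section 2.6 places the assessments "at visit 1 within 7 days of registration". Screening is the only earlier contact that the text describes.
- **What is measured at visit 1 (section 2.6).** "For participants enrolled in the study after screening, we will perform blood tests; ABI and brachial–ankle pulse wave velocity measurement", followed by the blood stasis questionnaire, blood pressure, body mass index, waist circumference and a record of treatments.
- **Biomarker primary outcome (section 2.7.1).** "Resistin, serum amyloid P component, C-reactive protein, and D-dimer are the candidate indicators". None of the four is a selection criterion.
- **Grouping (section 2.4.1).** Criterion 1 is a low ABI, or high triglycerides together with low HDL cholesterol. Criterion 2 is a blood stasis score of at least 9 out of 32. The score is also a primary outcome, and ABI, triglycerides and HDL cholesterol are secondary outcomes (sections 2.7.1 and 2.7.2).

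**The concern.** Last observation carried forward belongs to repeated-measures designs: a missing value at one visit is replaced by the same variable's value from an earlier visit. Here the comparison is made at the first visit after screening, which raises two separate problems.

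First, a variable measured for the first time at visit 1 has nothing to carry. The rule is then empty for that variable, and the article has no other. For a primary outcome, this leaves the handling of missing values to be settled after the data are in hand.

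Second, where an earlier value does exist, it may be the one that put the patient in the group. Patients selected for an extreme value tend to be less extreme when measured again. Carrying the selection value forward ignores that movement, so it exaggerates the difference between groups. It also counts the carried number as a real measurement, which makes the precision look better than it is.

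**Working it through.** The plan states no figure on this point that could be reproduced. Section 2.9 sets 100 participants without an effect size and mentions dropout without a rate. The check therefore has two parts.

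**Part 1: which outcomes have a value before visit 1?** This is read from sections 2.4.1, 2.6 and 2.7.

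| Outcome | Defines the groups? | Earlier value on the text | What the rule would do at visit 1 |
|---|---|---|---|
| Resistin, serum amyloid P component, C-reactive protein, D-dimer | No | None described | Nothing to carry |
| Blood stasis score, ABI, triglycerides, HDL cholesterol | Yes | Implied, because grouping needs them | Carry the value that sorted the patient |
| baPWV, total cholesterol, blood pressure, BMI, waist circumference | No | None described | Nothing to carry, or carry a value that did not select the patient |

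Visits after visit 1, if there are any, do not change the table, since the rule only carries forward.

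**Part 2: how large is the effect for the four grouping measures?** The documents give neither the missing fraction nor the screening-to-visit-1 correlation, so both are assumed and shown as ranges.

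Model: *s* is the standardised screening value on which the patient is grouped and *v* the visit-1 value, with correlation *r*. A fraction *m* of visit-1 values is missing at random in every group and is replaced by *s*. Let *D* be the group difference at screening.

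- True visit-1 difference: *r* × *D*
- Difference after carrying forward: (1 − *m*) × *r* × *D* + *m* × *D*
- Relative inflation: [(1 − *m*)*r* + *m*]/*r* − 1 = *m*(1 − *r*)/*r*

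The cut-off drops out of the ratio. Results:

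| *r* | *m* = 5% | *m* = 10% | *m* = 20% |
|---|---|---|---|
| 0.6 | 3.3% | 6.7% | 13.3% |
| 0.75 | 1.7% | 3.3% | 6.7% |
| 0.9 | 0.6% | 1.1% | 2.2% |

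For example, *r* = 0.6 and *m* = 20% give 0.20 × 0.4/0.6 = 13.3%. A simulation of 2,000,000 subjects grouped at *s* > 1 SD agrees: in that cell the difference rises from 1.089 to 1.234 SD, or 13.3%. In the mildest cell (*r* = 0.9, *m* = 5%) it rises from 1.631 to 1.640 SD, or 0.6%.

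The same effect on the scale of a single value: if a group is the top third of a normal distribution, its mean is 1.091 SD. With *r* = 0.8, each carried value exceeds the expected re-measurement by 1.091 × (1 − 0.8) = 0.218 SD on average. In the group mean this is multiplied by the missing fraction:

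- 5% missing: 0.218 × 0.05 = 0.011 SD
- 10% missing: 0.218 × 0.10 = 0.022 SD
- 20% missing: 0.218 × 0.20 = 0.044 SD

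The understatement of the standard error was not computed. Its direction follows from counting imputed values as observed, and its size again depends on the missing fraction.

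**The case against.** The strongest defence has four parts.

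1. **The visit schedule is in Table 1, whose contents were not available for this check.** Sections 2.2 and 2.8 mention follow-up, and section 2.10 calls the visit-1 comparison a basic analysis, so the rule may be meant for later visits. A biomarker might also have been measured in a screening sample. This stands as a limit on confidence. It does not rescue the rule as written, which covers every missing value while the only described comparison is at visit 1.

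2. **The text does not say that the grouping measures are taken twice.** If groups were assigned from the visit-1 values themselves, there would be nothing to carry and the selection argument would lapse. This also stands, so that half of the point is conditional. The natural reading is still that grouping values are known at selection, while section 2.6 lists the same measurements for participants already enrolled after screening.

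3. **Little may change in practice.** If no biomarker value can be carried, the analysis falls back to observed cases, as recommended below. For the grouping measures, separation is largely built in by definition. This is largely right and lowers the severity. It does not justify keeping a rule that cannot be followed for a primary outcome.

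4. **A multiple-imputation model is detail for an analysis plan.** Agreed; none is asked for here.

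A reader might also infer that every measure other than the biomarkers would inherit a selection value. The documents do not support this: baPWV, total cholesterol, blood pressure, BMI and waist circumference play no part in section 2.4.1. Nor should the 0.22 SD figure be read as the bias in the comparison, since it applies to each carried value and shrinks with the missing fraction. And carrying forward does not introduce regression to the mean; it leaves out the regression that re-measurement would show.

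**Conclusion.** The point holds in a limited form. On the text, the only stated missing-data rule cannot be applied to the four biomarkers at the only analysed visit. This part needs no numerical assumption, only that Table 1 lists no earlier biomarker measurement.

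For ABI, triglycerides, HDL cholesterol and the blood stasis score, the rule would carry the selection value, provided they are measured both at screening and at visit 1. The resulting inflation of the group difference is small to moderate: about 0.6% to 13% for correlations of 0.6 to 0.9 and 5% to 20% missing. It rests on a normal model with grouping on one variable at a time and values missing at random. Criterion 1 in fact combines three variables, so the figures are illustrative. An interval of about a week would argue for the higher correlations and hence the smaller effects, but the documents give no value.

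A reader might conclude that the group comparisons as a whole are invalid. The documents do not support that: the study is exploratory, the bias is confined to four measures that separate the groups by construction, and unfilled biomarker values would simply remain missing. It should be fixed at most, with moderate confidence.

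**What to change.** In section 2.10, remove last observation carried forward for the visit-1 comparison and state instead that:

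- each measure is analysed in participants with an observed visit-1 value, with the number missing reported by group;
- the four group-defining measures are neither carried forward nor imputed;
- multiple imputation is used only as a sensitivity analysis, if missingness is material, with its model left to the analysis plan.

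If the rule was meant for later visits, say so and name the visits and variables. It would also help to state whether the grouping measures are taken once or twice, because the second half of this point depends on it.

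The cost is about one sentence in the protocol and minor extra programming, with no new visits or samples. The downside is slightly smaller numbers for some measures: with 100 participants, 5% to 20% missing would leave 95 to 80 observed values for a measure.

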### Ethics and dissemination

2.11

The Institutional Review Board of the Dongguk University Ilsan Oriental Hospital (DUIOH-2018-09-001-007) approved the study. Written informed consent will be obtained from all study participants before enrollment in the study. The results will be published in a peer-reviewed journal and disseminated electronically and in print regardless of results.

## Discussion

3

This prospective observational study is designed to investigate the effectiveness of the diagnosis index for metabolic diseases with blood stasis by analyzing clinical data. Treating blood stasis is effective in treating metabolic diseases in traditional Korean medicine,^[8,11]^ but there is insufficient evidence regarding the effectiveness of the diagnosis index in metabolic diseases with blood stasis. Findings of this study will provide a summary of the current state of evidence regarding the effectiveness of the diagnosis index in managing metabolic diseases with blood stasis. In addition, this study is expected to provide a basis for clinical trials to confirm the efficacy of Korean medicine for treatments of metabolic diseases with blood stasis.
